**AMENDMENT #4**

We are adding the 34 research assistants that will be helping us to take the anthropometry measurments at the beginning and end of the protocol. They have all received CITI training. The first 17 students listed on the amendment form passed on 12/10/08. The next 18 passed CITI training on 12/17/08.

**AMENDMENT #5**

We would like to run several additional assays on the already stored blood samples from our trial. Our consent form contains the following text:

"I agree that any left over blood or urine sample can be stored for future additional research on vitamin D, infection, asthma, eczema, childhood growth and development."

The additional assays fall under the purview of the above statement because they are all relevant to infection. Only parents and children who checked yes will be included.

TGF beta 1 & 2

sIGA-

Cortisol

hsCRP

We would also like to request that [name] be added to the study staff to do the analytic programming. [name]'s CITI certificate is attached.

**AMENDMENT #6**

We would like to run several additional assays on the already stored blood samples from our trial. Our consent form contains the following text:

"I agree that any left over blood or urine sample can be stored for future additional research on vitamin D, infection, asthma, eczema, childhood growth and development."

The additional assays fall under the purview of the above statement because they are all relevant to childhood growth and development. Only parents and children who checked yes will be included.

Estrogen metabolites panel

(E1, E2, E3, 16KE2, 16aE1, 16epiE3, 17epiE3, 3ME1, 2ME1, 4ME1, 2ME2, 4ME2, 2OHE1, 2OHE2, and 4OHE1)

**STATISTICAL PLAN AND CHANGES RELEVANT TO NEJM ANALYSIS**

**Analysis Plan for Supplementation Study and Fortification Study Vitamin D and Growth Paper**

*Goal*: to test the extent to which Vitamin D affects physical growth in children (weight, height, and BMI) in Vitamin D versus Placebo or Mongolian +D versus Mongolian regular milk.

1. Check the distribution of the outcome variables

- Run proc univariate and boxplots of each of the following for everyone:
  - Weight at Visit 1
  - Height at Visit 1
  - BMI at Visit 1
  - Weight at Visit 2
  - Height at Visit 2
  - BMI at Visit 2
  - Delta Weight
  - Delta Height
  - Delta BMI
- Repeat for each intervention arm separately
- If things are looking non-normal, try a log transformation and rerun proc univariate and boxplot
- STOP: let’s check degree of missingness in each delta
- STOP: check with [name], [name] and [name] to check normality and decide on any transformation

3. Re-run descriptive statistics from IGF analysis (Fortification Study only) to confirm accuracy for growth variables also evaluating combined 25OHD levels.

- Create table with all information
- (columns by treatment arm)

4. Missingness: for now, let’s do complete case analysis, unless step 2 reveals atrocious missingness, in which case we might want to create missing indicators

5. Then we can start some modeling.

- PROC REG’s for each of the deltas as dependent variables (weight, height, BMI)
  - Create indicator variables for the following interventions: Vitamin D and Placebo for Supplementation Study. Mongolian Regular, Mongolian milk + D for Fortification study. Use the Placebo and Mongolian regular arm as the referent, respectively.
  - Crude model with intervention only
  - Second model adjusted for age, school (Fortification study only), and gender
  - Third model additionally adjusted for compliance [as proportion of intervention received🡪completion
- Also model plasma 25OHD individual change against three growth delta variables (weight, height, BMI)
  - Crude model with 25OHD change only
  - Second model adjusted for intervention arm
  - Second model adjusted for age, school (Fortification study only), and gender and intervention
  - Third model additionally adjusted for compliance [as proportion of intervention received🡪completion

6. Repeat all PROC REG models for the treatment group contrasts with PROC MIXED models

- Crude model with intervention only

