Treatment regimen: Subjects will be randomly assigned to receive a daily oral dose of one of two treatments from enrollment until the end of the study: (1) vitamin D (800 IU per day), or (2) placebo every school day for total nine months. All the experimental tablets will be identical in color but number-coded. The daily dose of vitamin D (800 IU) that we will use is well under the tolerable upper limit (TUL) of 2000 IU set by the institute of Medicine for children*, and is well below the level of human toxicity. The only known cases of toxicity have involved vitamin D intake greater than 40,000 IU/day. (21). **Standing Committee on the Scientific Evaluation of Dietary Reference Intakes FaNB, Institute of Medicine: Dietary Reference Intakes for Calcium, Phosphorus, Magnesium, Vitamin D, and Fluoride. National Academy Press, Washington, D.C., 1997. Available online at <http://books.nap.edu/openbook.php?record_id=5776&page=285>

Participant compliance monitoring: Substantial consideration has been given to the issue of adherence to the vitamin D intake protocol. First, 14 days after the participant is scheduled to begin taking supplementation they will be called to assess for any symptoms of toxicity. At that time, a series of brief questions will be asked to determine if the participant is having difficulty with adherence, and barriers will be addressed. Any participants who report having difficulty will be contacted again in 3 days to assess adherence and identify any additional strategies that might enhance adherence. Second, at the beginning of each month we will contact all participants and remind them that the next month of supplementation is about to begin, and address any concerns. Finally, children will take the supplementation in the class under teacher’s supervision. We will also collect any remainder pills and count those pills. Finally, we will assess compliance by self-report.

Blinding: Placebo will be provided in tablets, identical in size and appearance to vitamin D tablets. Blinded study medication will be packaged in bottles containing tablets to provide sufficient supply for each month, with overage. All site personnel will be blinded to the treatment arm assignment.

Receiving, storage, dispensing and return: Study subjects will be instructed to return all unused study supplementation in the bottle in which it was dispensed. The study research associate will be responsible for dispensing the study supplementation to participants

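### The growth plan prints the outcome changes by intervention arm before the team decides, by judgement, on the scale of analysis, and it leaves the missing-data rule provisional until after that output

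*Supplement*

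**What the plan says.** The relevant text is the Analysis Plan for Supplementation Study and Fortification Study Vitamin D and Growth Paper. The order of steps is:

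1. Step 1 opens with "Run proc univariate and boxplots of each of the following for everyone". The list covers weight, height and BMI at both visits and the three changes.
2. The next bullet is "Repeat for each intervention arm separately".
3. Then comes the trigger for a transformation: "If things are looking non-normal, try a log transformation and rerun proc univariate and boxplot".
4. Two hold points follow. One is to "check degree of missingness in each delta". The other is to consult named colleagues "to check normality and decide on any transformation".
5. Step 3 (Fortification Study only) makes a descriptive table with "columns by treatment arm".
6. Step 4 says "for now, let’s do complete case analysis", with missing indicators as a possible alternative if missingness proves very bad. No threshold is given.
7. Step 5 begins the regressions of the three changes on intervention arm, and step 6 repeats the treatment contrasts with mixed models.

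Step 4 refers back to a step 2, but the printed numbers go from 1 to 3. The two hold points are probably that step, and the order is the same either way.

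On blinding, the Supplementation Study protocol says "All site personnel will be blinded to the treatment arm assignment". The Fortification Study describes itself as partially blinded. Neither mentions the analysts.

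**The concern.** The changes summarised by arm in step 1 are the dependent variables compared between arms in step 5. PROC UNIVARIATE gives the mean, median and spread in each arm, and boxplots show the centres side by side. Whoever settles the scale at the second hold point therefore already has the crude treatment contrast to hand.

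That would matter little if a fixed rule settled the scale. Here the trigger is whether the data look non-normal, and the decision is made in discussion. The option is also underspecified. The plan does not say whether the log is taken of the visit values or of the change, and a change in weight or BMI can be zero or negative, where a log does not exist. The missing-data rule has a default and one named alternative, but the default is provisional and the trigger for leaving it is undefined.

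At stake is the reading of the p-values for three outcomes in two studies. A reader cannot tell from the plan whether the reported scale would have been chosen without sight of the arm difference.

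**Working it through.** **Order of steps.** The documents give no figure for this point, so there is none to reproduce. The textual check has three parts:
- The by-arm output comes before both hold points.
- The variables shown by arm are the ones tested.
- No section of either protocol or of the plan provides for coded arms, a blinded analyst or a decision on pooled data. The Fortification protocol's own Statistical Analysis section also lets the data decide on transformation, without saying pooled or masked.

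The missingness check is not stated to be by arm. What can be said of it is only that it is listed after the by-arm output.

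**How much the visible contrast could matter.** Inputs from the documents:
- alpha 0.05 (two-sided is assumed);
- 120 children in the Supplementation Study (Amendment #1), taken as 60:60, which is an assumption;
- 150 fortified against 100 unfortified Mongolian milk (Fortification Study Design).

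The documents do not give the distribution of the changes, so every distribution below is an assumption. Under no treatment effect, let p_raw and p_log be the t-test p-values on the two scales. The quantities compared are:
- scale fixed in advance: P(p_raw < 0.05) or P(p_log < 0.05);
- scale chosen on normality alone: P(p_chosen < 0.05);
- favourable scale always chosen: P(min(p_raw, p_log) < 0.05).

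| Assumed changes under no effect | Rule | Type I error |
|---|---|---|
| Lognormal changes (SD of log 0.5 or 1.0) or growth proportional to baseline; 20,000 runs | either scale, fixed | 4.2–5.2% |
| Check with a normality-based choice | normality alone | near 5% |
| Difference of logged visit values against raw change | smaller p always | 5.3–6.1% |
| Gamma changes, logged directly | smaller p always | 5.9–7.2% |

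Other assumed inputs give similar answers for the last rule:
- Normal changes with mean/SD 1.5/1.0 cm, 1.0/1.0 kg and 0.1/0.5 BMI units (logs taken at the visits, 6,000 runs) gave 5.2% for height, 6.2–6.6% for weight and 5.8–5.9% for BMI.
- Proportional growth gave 7.3% at both sample sizes.
- Lognormal changes gave 6.5–6.8% at 60:60 and 6.7–7.5% at 150:100.

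Monte Carlo standard errors near 5% are √(0.05 × 0.95 / 20,000) = 0.15 points and √(0.05 × 0.95 / 6,000) = 0.28 points. Differences of a few tenths between scenarios therefore carry no meaning.

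The gamma and lognormal models make every change positive and log it directly. This cannot be done with real changes that include zero or loss; the Fortification protocol's Table 3 itself grades weight loss. Differencing logged visit values is the workable version. It gave the smaller inflation when the changes were normal, and 7.3% when growth was proportional to baseline.

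**The case against.** The best reply is that looking within arms is sound practice. Regression and t-test assumptions concern distribution and variance within groups. A pooled plot can hide unequal variances or an outlier confined to one arm, and the 25(OH)D models in the same plan keep separate variance estimates by treatment group. That stands: the fault is in the timing and the unmasked labels, and by-arm plots do have a use.

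Second, the stated reason for transforming is distribution, pooled output comes first, and log is the only transformation named. This also stands. A reader might infer that the error rate exceeds 5%, but the documents support only that it could, if the choice followed the contrast.

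Third, a reader might infer that the Supplementation Study's double blind is given up at the analysis stage. The text does not support this. The promise covers site personnel, no analyst blind is offered, and Amendment #2 of that study expects unblinding once the questionnaire data are in.

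Fourth, the Wilcoxon fallback appears in the protocols' analysis sections and not in the growth plan, so it should not be counted as a further option opened by these steps.

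Finally, masking may come too late for the Fortification Study. Step 3 re-runs descriptive statistics from an IGF analysis, and the interaction models refer to a term created before. This limits what masking can achieve there, and it makes a written rule the more important safeguard.

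**Conclusion.** The point holds as one of avoidable exposure. The plan makes the crude contrast in weight, height and BMI change visible before a judgement-based choice of scale, and it leaves the missing-data default open until after the same output. It does not show that either choice was driven by the effect.

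The possible size is modest. Type I error is near 5% if normality alone decides. It is roughly 5.3–7.2% per outcome if the better-looking scale is always taken, with 5.2% and 7.5% as the extremes across the other distributions tried. These figures rest on assumed distributions, an assumed 60:60 split and two-sided tests. They concern the transformation only; the missing-data part was not quantified and is the weaker half. The change is worth making because it closes a route to bias at almost no cost, and not because the results are shown to be wrong.

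**What to change.** - Move the by-arm bullet in step 1 to after both hold points. Alternatively, run it with masked arm labels on values centred within arm, or on residuals, so that spread and outliers show but the difference in centre does not.
- Take both decisions on pooled data, or on residuals from a model without the arm term (age and gender; also school and classroom in the Fortification Study).
- State the transformation exactly: log the visit values, then difference them.
- Give a criterion for using the transformation, and a stated level of missingness at which complete-case analysis is replaced, together with the replacement.
- Record the decisions with a date, then merge the arm code.
- Keep the by-arm plots afterwards as diagnostics of unequal variance and outliers.
- For the Fortification Study, also write down the scale and the missing-data rule before growth changes are viewed by arm, and hold back the growth part of the by-arm table in step 3 until then.

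The cost is a change in the order of programming and a short dated note. No data or analyses are lost. If the growth changes have already been seen by arm, the paper should say so and report both scales.

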5. Compare “fortified milks” to daily supplements (daily is referent group; combine UHT and Mongolian fortified as one fortified group)
   1. 25OHD delta = fortified milk + seasonal + Mon regular
   2. 25OHD delta = fortified milk + seasonal + Mon regular + school + gender + age as fixed effects, and classroom as random effect
   3. 25OHD delta = fortified milk + seasonal + Mon regular + school + gender + age + completion as fixed effects, and classroom as random effect

6) Interaction models with indicator interaction and all vit D intervention groups: Exclude unfortified milk from these. Create 0/1 interaction terms between Intervention arm and v1_25OHD_below10. (the same interaction you created earlier). These should include intercept.

a. 25OHD delta = UHT + Mon fortified + seasonal + daily + school + gender + age + v1_25OHD_below10 + the interaction as fixed effects, and classroom as random effect

(here we add in the main effect of v1_25OHD_below10)

b. 25OHD delta = v1_25OHD_below10 + school + gender + age, and classroom as random effect
